#### Assessment of clinical efficacy and safety

The clinical efficacy assessment will include evaluating effects of the two fixed ESA doses on the composite of all-cause mortality, non fatal stroke, non fatal myocardial infarction, and hospitalization for acute coronary syndrome, transient ischemic attack, non-planned coronary revascularization procedures and peripheral revascularization procedures. In addition, secondary clinical end-points will include each component of the primary end-point, cardiovascular mortality, vascular access thrombosis, and other safety measures, including seizures and hypertension.

#### Quality of life assessment

Quality of life (QoL) will be assessed at baseline and every six months thereafter by administration of the KDQOL-SF™ 1.3 questionnaire. This self-administered tool includes 2 QoL instruments, the SF36 and the KDQOL, which are generic and CKD-specific QoL measures, respectively. The KDQOL-SF™ 1.3 questionnaire consists of 18 scales: 8 from the SF-36 questionnaire [13,14] (physical function, role limitations caused by physical health problems, role limitations caused by emotional health problems, bodily pain, general health perception, vitality, social activities, and mental health) and 10 from the KDQOL questionnaire [15] (symptoms, effects of kidney disease on daily life, work status, cognitive function, quality of social interaction, sexual function, sleep, social support, patient satisfaction).

#### Clinical feasibility assessment and cost-efficacy analysis

The clinical feasibility of the two therapeutic strategies will be assessed by reviewing the following: number of patients in each arm who maintain stable Hb levels between 10.0 and 12 g/dL, without need for > 50% change in the allocated dose of ESA; number of ESA dose variations from time of randomization to time of Hb level stabilization (between 10.0-12.0 g/dL); average variation of allocated ESA dose (IU/week for erythropoietins or microgram/week for darbepoetin) in the two arms; average ESA dose variation based on weight and body mass index; time from randomization to the first ESA dose variation; time from randomization to Hb level stabilization (between 10.0-12.0 g/dL); number of blood transfusions and number of patients requiring one or more blood transfusion.

In addition the cumulative in-centre and out-centre costs of managing dialysis patients allocated to the high versus low fixed ESA doses will be assessed in a subset of the overall population.

### Statistical methods

#### Sample size

The sample size for the C.E.DOSE trial is estimated based on the following assumptions:

a) Annual incidence of the primary composite end-point of 15%, based upon data from existing trials [5,16];

b) Expected relative risk reduction in the primary composite end-point with the experimental intervention (low ESA dose) of 15% (hazard ratio = 0.85) based upon evidence from randomized trials showing increased risk of death and adverse vascular outcomes in higher Hb levels of approximately 15% [7];

c) 80% power using an alpha of 0.05;

d) A dropout rate of 5%.

Given these assumptions, 2204 individuals will be recruited. If fewer patients are randomized or the event rate of the primary endpoint is lower than expected, the duration of follow-up will be extended.

#### Data analysis

Analysis will be by the intention-to-treat principle. The incidence rate of events in the high dose versus the low dose ESA groups will be estimated using Kaplan-Meier curves. Log-rank test will be used to compare the two curves [17].

Additional multivariate analyses will be performed using a Cox proportional hazards model [17]. The proportional hazards assumption will be checked by graphical inspection of log (-log [survival]) plot. Analyses will be performed for assessment of the efficacy of study interventions (high doses or low doses of ESA) on any of the end-points of this study, including quality of life and costs. The treatment effect on outcomes, quality of life, and costs will be also evaluated through subgroup-analysis based upon a series of potential effect modifiers (baseline information) including socio-demographic factors (gender, age, ethnicity, marital status, education, occupational status), presence or absence of cardiovascular risk factors (diabetes mellitus, hypertension, cigarette smoking, family history of cardiovascular disease), presence or absence of previous major cardiovascular event, presence or absence of other major concomitant illness, type of ESA administered, average ESA dose administered during the study, metabolic control (quartiles of total/LDL/HDL-cholesterol and HbA1c), other cointerventions (iron, vitamin D or vitamin D analogues, phosphate binders, calcimimetics, antihypertensive agents, statins, anticoagulants), baseline and end of treatment levels of calcium, phosphorus, iron, parathyroid hormone; Kt/V, dry weight, dialysis blood flow rate, interdialytic weight gain, type of dialysis (bicarbonate-dialysis, high versus low flux, hemodiafiltration, online hemodiafiltration, hemofiltration, acetate-free biofiltration), dialysis duration (minutes per dialysis session) and dialysis vintage (months). Existing trends in the efficacy based upon these subgroup analyses will be tested with the Mantel-Haenszel test for each of these covariates. A chi-square test will be used to assess heterogeneity of observed effects of interventions.

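### Kaplan-Meier is the only incidence estimator named and is not confined to the primary composite; used for secondary clinical endpoints that death precludes, it would overstate absolute incidence

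*Protocol article*

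**What the plan says.** In the protocol article, *Data analysis* states: "The incidence rate of events in the high dose versus the low dose ESA groups will be estimated using Kaplan-Meier curves". It continues: "Log-rank test will be used to compare the two curves". Cox models follow as additional multivariate analyses. The next statement of scope is that effects will be analysed "on any of the end-points of this study, including quality of life and costs". No sentence restricts the Kaplan-Meier estimate to the primary endpoint, and no other estimator of incidence is named.

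*Assessment of clinical efficacy and safety* defines the primary endpoint as a "composite of all-cause mortality, non fatal stroke, non fatal myocardial infarction" and hospitalization for several cardiovascular causes. It adds that "secondary clinical end-points will include each component of the primary end-point, cardiovascular mortality, vascular access thrombosis" and other safety measures.

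*Study design* says that the incidence of all events will be measured at follow-up visits, and it glosses events in brackets as outcomes. The article does not mention competing risks or cumulative incidence functions, or say how deaths are treated when the endpoint is not death itself.

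**The concern.** A patient who has died can no longer have a non-fatal stroke, a non-fatal infarction, a cardiovascular admission or an access thrombosis. A patient who has died of a non-cardiovascular cause can no longer die of a cardiovascular one. Kaplan-Meier with such deaths censored treats these patients as if they remained at risk. One minus Kaplan-Meier then describes a setting in which the competing death does not occur, and it exceeds the proportion of patients who actually have the event whenever the competing death hazard is above zero.

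Death is unlikely to be rare here. The patients are on hemodialysis, the composite that includes all-cause death is expected at 15% per year, and 1194 events are planned in 2204 patients (1194/2204 = 54%).

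What is at stake is the reported absolute risk of each affected endpoint and the absolute differences between arms. If the doses differ in mortality, the two arms' curves are inflated by different amounts.

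**Working it through.** **The plan's own figure.** Freedman's formula with the stated "hazard ratio = 0.85", 80% power and two-sided alpha 0.05 (the article does not state the sidedness) gives 7.849 × (1.85/0.15)² = 1193.9, that is, the planned 1194 events. This count concerns the composite, in which death is an event, so competing risks do not alter it.

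**Inputs for the check**
- From the documents: recruitment over 12 months and about 4 years of follow-up after the last patient, hence 4 to 5 years per patient and T = 4.5 on average (*Study design*); "Annual incidence of the primary composite end-point of 15"% (*Sample size*).
- Assumed, because the documents give neither: endpoint hazard h of 2% or 3% per year; competing death hazard d of 5% to 12% per year; both constant.

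**Formulas**
- Deaths censored: 1−KM = 1 − exp(−hT)
- Death as competing event: CIF = h/(h+d) × [1 − exp(−(h+d)T)]

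**Example, h = 3%**
- 1−KM = 1 − exp(−0.135) = 12.6%
- d = 5%: CIF = (0.03/0.08) × [1 − exp(−0.36)] = 11.3%
- d = 12%: CIF = (0.03/0.15) × [1 − exp(−0.675)] = 9.8%

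| h per year | d per year | 1−KM | CIF | Ratio |
|---|---|---|---|---|
| 2% | 5% | 8.6% | 7.7% | 1.11 |
| 2% | 8% | 8.6% | 7.2% | 1.19 |
| 2% | 12% | 8.6% | 6.7% | 1.29 |
| 3% | 5% | 12.6% | 11.3% | 1.11 |
| 3% | 8% | 12.6% | 10.6% | 1.19 |
| 3% | 12% | 12.6% | 9.8% | 1.29 |

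**Plausibility of the upper end.** A death hazard of 12% per year would be 12/15 = 80% of the composite rate. If deaths make up 40-70% of the composite (0.40 × 15% = 6% to 0.70 × 15% = 10.5% per year), the overstatement for non-fatal endpoints is about 13-25%.

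**Cardiovascular death.** Take it as half of total mortality of 6-15% per year, so h = d. At 3% each, 12.6% against 11.8% (about 7% too high). At 7.5% each, 28.6% against 24.5% (about 17% too high).

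**Difference between arms.** The hazard ratio of 0.85 is stated for the composite only. As an illustration, apply it to both the component (3% against 2.55% per year) and death:
- 1−KM: 12.63% − 10.84% = 1.79 percentage points, whatever the death rate
- CIF, d = 5% (4.25% in the low-dose arm): 11.34% − 9.89% = 1.45 points
- CIF, d = 12% (10.2% in the low-dose arm): 9.82% − 8.73% = 1.09 points

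Under these assumptions Kaplan-Meier shows a risk difference 0.34 to 0.70 points too large.

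**The case against.** The strongest objection is about scope. The Kaplan-Meier sentence speaks only of events and of one pair of curves. The phrase "high doses or low doses of ESA) on any of the end-points of this study" comes later, after the Cox model, and names no method. It also takes in quality of life, which Kaplan-Meier does not suit, so it cannot by itself assign Kaplan-Meier to every endpoint. A reader might infer that the protocol expressly prescribes one estimator throughout; it does not. On this view, what remains is an omission of the kind a condensed article leaves to the analysis plan.

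Part of this stands: use for the secondary endpoints is read from the text, not stated in it. But the article is not silent on the estimator. It names one, leaves it unrestricted, equates events with outcomes in *Study design*, and lists mostly secondary clinical endpoints for which that estimator is unsuitable. An analysis plan that followed the article would carry the problem over.

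The second objection stands in full. The planned log-rank and Cox comparisons, with deaths censored, are valid comparisons of cause-specific hazards. A reader might infer that the treatment comparisons are invalid; the fault lies only in absolute incidence and absolute differences.

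Two further inferences lack support:
- That inflated risks would enter the cost-effectiveness analysis. The article lists that aim and describes collecting cumulative costs in a subset, but does not say that Kaplan-Meier risks are an input.
- That time to hemoglobin stabilization is affected in the same way. It is listed among feasibility measures to be reviewed, with no estimator, and the calculation above does not represent it.

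**Conclusion.** The point holds for the secondary time-to-event clinical endpoints other than all-cause death, on the natural but inferred reading that Kaplan-Meier applies to them. The direction of the bias follows from the estimator. Its size does not come from the documents: about 11-29% relative for non-fatal components rests on assumed constant hazards of 2-3% per year for the endpoint and 5-12% per year for death over 4.5 years, and about 7-17% for cardiovascular death rests on the half-of-mortality assumption. The distortion of risk differences is illustrative, since the article specifies no separate mortality effect.

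A reader might infer that the main result is biased. It is not: the primary composite, all-cause mortality, the 1194-event target and the sample size of 2204 are untouched. This is a correction worth making to secondary reporting, not a threat to the trial's main conclusion.

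**What to change.** In *Data analysis*, confine Kaplan-Meier to the primary composite and all-cause death. For the other time-to-event clinical endpoints, report cumulative incidence by the Aalen-Johansen estimator, with death as the competing event (non-cardiovascular death, for cardiovascular mortality). Keep the planned log-rank and Cox analyses and label them as cause-specific comparisons. Show the death curves by arm beside each cumulative incidence curve, so that a difference in incidence can be read against any difference in mortality.

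If Kaplan-Meier was meant only for the primary composite, one sentence saying so and naming the estimator for the rest is enough. The cost is a change of wording here or in the analysis plan, and standard software. No further patients, data or follow-up are needed.

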### Study design

This will be a pragmatic, multicenter, centrally randomized, controlled trial (Figure 1) based upon the intention-to-treat principle. To achieve allocation concealment, randomization will be carried out centrally by the coordinating study center. Independent of baseline Hb level, participants will be allocated to ESA 4000 IU/week intravenously versus 18000 IU/week intravenously of erythropoietin alfa, beta, or equivalent doses of any other commercially available agent (including darbepoetin alfa, C.E.R.A. or biosimilars and other agents, which may become available). Randomization will be stratified by enrolling center and treatments will be assigned by random permuted blocks of six patients.

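### An unadjusted log-rank test is valid and delivers the planned 80% power, but adjusting for age, diabetes and previous cardiovascular event would cheaply add some

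*Protocol article*

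**What the plan says.** All references are to the protocol article.

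- **Test of the arms (Data analysis).** Kaplan-Meier curves are estimated by arm, and "Log-rank test will be used to compare the two curves". No strata or covariates are mentioned. The text does not label this test primary or unadjusted. That is the plain reading, because it is named first and matches the sizing.
- **Covariate model (Data analysis).** "Additional multivariate analyses will be performed using a Cox proportional hazards model". It is ranked second.
- **Baseline variables (Data analysis).** Subgroup analyses use "a series of potential effect modifiers (baseline information) including socio-demographic factors (gender, age, ethnicity" and others), "presence or absence of cardiovascular risk factors (diabetes mellitus, hypertension" and others), and "presence or absence of previous major cardiovascular event". So age, diabetes and cardiovascular history are all to be recorded, but their only stated use is as effect modifiers.
- **Balance by design (Study design).** "Randomization will be stratified by enrolling center". None of the three variables is a stratification factor.
- **Sizing (Sample size, Study design).** "hazard ratio = 0.85" and "80% power using an alpha of 0.05", with 2204 patients and follow-up until 1194 events.

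**The concern.** The composite includes all-cause death and major cardiovascular events. Age, diabetes and an earlier major cardiovascular event can be expected to predict it, although the documents do not say how strongly. About 54% of patients are expected to have an event (1194/2204 = 0.542). At that event proportion, leaving strong predictors out of a survival comparison makes the hazard ratio noticeably closer to 1 than the hazard ratio for patients of given risk, and the crude test has less power than an adjusted test on the same data.

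The plan is sized at 80% power for a modest effect. Any power that can be had from data already collected, without more patients or longer follow-up, is worth taking.

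**Working it through.** **1. Reproduce the plan's figure.** Inputs: hazard ratio 0.85, alpha 0.05, power 80% (Sample size); 1:1 allocation (Abstract).

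- Freedman: events = (1.960 + 0.842)² × [(1 + 0.85)/(1 − 0.85)]² = 7.849 × 152.1 = 1194. This matches the stated count exactly.
- Schoenfeld: 4 × 7.849/(ln 0.85)² = 1189.
- One-sided alpha would give 941 (Freedman) or 937 (Schoenfeld), so the plan is two-sided.
- Power of the log-rank test at 1194 events and hazard ratio 0.85 is 80.0% (Freedman) or 80.2% (Schoenfeld).

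The sizing is that of an unadjusted log-rank test, and the test delivers it.

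**2. Add the covariates, holding the marginal hazard ratio at about 0.85.** This was simulated with 2204 patients, 1:1 allocation, 12 months' accrual and analysis at the 1194th event. The log-rank test is compared with the treatment term of a Cox model containing age, diabetes and previous event. Assumptions that are not in the documents: diabetes in 30%, previous event in 35%, and the prognostic hazard ratios in the first column (per SD of age / diabetes / previous event). Where two figures are given, they come from separate sets of 2000 and 4000 simulated trials, with slightly different conditional hazard ratios. The very strong case was run once, with 2000.

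| Assumed strength | Conditional HR matching marginal 0.85 | Log-rank power | Adjusted power | Gain (points) |
|---|---|---|---|---|
| Weak, 1.3/1.3/1.4 | about 0.845 | 79.6%, 78.9% | 82.6%, 81.4% | 3.0, 2.5 |
| Moderate, 1.5/1.4/1.6 | about 0.840 | 79.5%, 78.8% | 84.4%, 84.4% | 4.9, 5.6 |
| Strong, 1.8/1.6/2.0 | about 0.825 | 81.6%, 80.0% | 90.8%, 90.6% | 9.2, 10.6 |
| Very strong, 2.0/2.0/2.0 | 0.815 | 81.2% | 94.1% | 12.9 |

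With no prognostic effect the two tests have equal power (80.3% and 80.6%). The Monte Carlo standard error of a power near 80% is √(0.8 × 0.2/2000) = 0.9 points, or 0.6 points with 4000 runs.

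**3. Cross-check by formula.** Schoenfeld power at 1194 events is Φ(½√1194 × |ln HR| − 1.960), and ½√1194 = 17.28.

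- Conditional HR 0.8447: Φ(17.28 × 0.1688 − 1.960) = Φ(0.956) = 83%.
- Conditional HR 0.840: Φ(17.28 × 0.1744 − 1.960) = Φ(1.052) = 85%.
- Conditional HR 0.8265: Φ(17.28 × 0.1906 − 1.960) = Φ(1.332) = 91%.

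These agree with the simulation to within about 2 points. Read the other way, 80% power for the adjusted test would need roughly 1103, 1033 and 865 events in these three cases, against 1194.

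**4. Type I error.** In 3000 null trials with moderate predictors, rejection was 5.5% (log-rank) and 5.7% (adjusted Cox). The standard error is √(0.05 × 0.95/3000) = 0.4 points. Both are close to 5%, so the gain is not bought with false positives.

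**The case against.** **The log-rank test is a legitimate choice.** It is valid, it matches the sizing, and an unadjusted comparison is common in a pragmatic trial. This stands in full: nothing in the plan is wrong or contradictory here. What remains is that a better use of the same data is available.

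**A reader might infer that the trial is underpowered.** If 0.85 were the effect for a patient of given covariates, simulated log-rank power would be about 76%, 75%, 66% and 60% from weak to very strong predictors, against 78–81% adjusted. The documents do not support that reading. The Sample size section takes 0.85 from pooled randomized evidence, which the Background reports as relative risks with no mention of covariate adjustment, and the event count is the log-rank count for that value. On the marginal reading, log-rank power stays at about 79–82% in every scenario. A hazard ratio nearer to 1 without covariates is then no bias either, since it is the marginal effect that is being estimated.

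**A reader might also fault the Cox model for not naming its covariates, or see room to choose between two answers.** A condensed article may leave that list to the full protocol or the SAP, and calling the Cox model additional already ranks it below the log-rank test. Neither is part of this point.

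**The size rests on assumption.** This is true. The documents give no prevalences and no prognostic hazard ratios, so the gain can be stated only as a range that starts at zero.

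**Conclusion.** This is a cheap improvement, not an error. The log-rank test reaches the planned 80% power at 1194 events if 0.85 is the marginal hazard ratio. At the same number of events, adjustment for the three baseline variables would add up to about 3 points of power if they are weak predictors, 5–6 if moderate and about 9–11 if strong. It adds nothing if they are not prognostic. The direction held in every scenario with prognostic covariates. The size depends on assumed prevalences and strengths, and on a simulation with exponential event times and proportional hazards.

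**What to change.** In the Data analysis section, before unblinding, state that the primary test is the treatment term of a Cox model with three fixed baseline covariates: age (continuous), diabetes and previous major cardiovascular event. Keep the Kaplan-Meier curves and the unadjusted log-rank test as a named supportive analysis. The 1194-event target can stay as it is.

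The cost is about one sentence, and no new data are needed because all three variables are already listed as baseline information. The drawback is interpretive. The adjusted hazard ratio is conditional on the covariates and will tend to lie further from 1 than the marginal one used for sizing (for example about 0.84 against 0.85 with moderate predictors). The crude hazard ratio should therefore be reported beside it, and the plan should say which effect each one estimates.

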**Figure 1 F1:**
[figure not shown]
**Flow chart describing the selection, randomization and follow-up process of the Clinical Evaluation of the Dose of Erythropoietins (C.E. DOSE) trial**.

As there are no previous studies relating to the benefits/harms of different ESA doses for the anemia of ESKD, we established two fixed experimental doses according to the following criteria, based upon available data:

1. In the antecedent Hb target trials conducted in CKD patients [4-6], patients randomized to high (12-14 g/dL) and low (9.5-11.5 g/dL) Hb targets received between 20000 to 30000 IU/week and between 0 to 10000 g/dL IU/week of EPO, respectively.

2. In the 2004 United States Renal Data System report, 50% of hemodialysis patients incident to ESRD therapy in 1998 and followed for one year, had Hb levels between 10-13 g/dL and received more than 13000 IU/week of EPO, in particular 25% received from 13.944 to 21692 IU/week and 25% more than 21.692 IU/week of EPO [11].

Based on these assumptions the two selected experimental doses will maximize study efficacy. We will also have a safety mechanism within the trial to ensure that, after allocation to treatment, Hb values do not fall outside the safety range (of 9.5 g/dL-12.5 g/dL). A hemoglobin value above or below this range will trigger a change in the ESA dose. The prescribed ESA dose will be gradually increased or decreased by 25% until Hb values return to between 9.5 and 12.5 g/dL.

We expect recruitment to last 12 months and follow-up will be completed after 1194 cardiovascular events have occurred, which is expected to be approximately 4 years after the last patient is enrolled.

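### Randomization is stratified by centre, but the log-rank test named for the main comparison gives centre no role: a conditional loss of efficiency, not an error of validity

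*Protocol article*

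**What the plan says.** Study design: "Randomization will be stratified by enrolling center and treatments will be assigned by random permuted blocks of six patients".

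Data analysis: after Kaplan-Meier estimation by arm, "Log-rank test will be used to compare the two curves". Modelling comes second: "Additional multivariate analyses will be performed using a Cox proportional hazards model". No covariates are given for that model. The long list of factors in the same section is a list of possible effect modifiers for subgroup analysis. Centre is not on it.

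Sample size: the effect is given as "low ESA dose) of 15% (hazard ratio = 0.85", with "80% power using an alpha of 0.05". The stopping point is in Study design: "follow-up will be completed after 1194 cardiovascular events have occurred".

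The article states neither the number of centres nor any between-centre variation in event rate.

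**The concern.** Blocking within centres balances the arms inside each centre. An analysis that compares patients only within centres benefits from this. A test on two pooled curves does not, because its variance is calculated as if allocation had ignored centre. When centres differ in event rate, two things follow:

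- The pooled (marginal) hazard ratio lies closer to 1 than the within-centre hazard ratio.
- The pooled test statistic varies less than its nominal variance says, so the test is conservative.

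Both reduce power. The planned number of events has no reserve to absorb this. There is some reason to expect centres to differ: the Background describes anaemia practice as very variable, Study design leaves co-interventions to the treating physician, and Study population admits several dialysis modalities. None of this gives a size for the variation.

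**Working it through.** **Step 1. The plan's own event number.** Inputs from Sample size: hazard ratio 0.85, power 80%, alpha 0.05. Sidedness is not stated; two-sided is assumed here.

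- Freedman: D = (1.96 + 0.8416)² × [(1 + 0.85)/(1 − 0.85)]² = 7.849 × 152.1 = 1194. The stated figure is reproduced exactly.
- Schoenfeld: D = 4 × 7.849/(ln 0.85)² = 31.40/0.02641 = 1189.
- Power at 1194 events (Schoenfeld): Φ(√1194/2 × 0.1625 − 1.96) = Φ(0.848) = 80.2%.

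These formulas contain no term for centre differences, and 80.2% leaves no margin.

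**Step 2. Simulation of the two tests.** From the article: 2204 patients, 1:1, blocks of six within centre, one year of accrual, analysis at the 1194th event. Assumed:

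- the 0.85 applies within centres;
- the 15% annual incidence belongs to the high-dose arm (hazard −ln 0.85 = 0.1625 per year);
- dropout is about 5% over five years;
- there are 30, 60, 100 or 150 centres of equal size;
- centre effects are lognormal, with the SD of the log hazard from 0 to 0.7.

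With 3000 trials per scenario, the Monte Carlo standard error is √(0.8 × 0.2/3000) = 0.7 points for each power figure. Both tests were run on the same simulated trials.

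Power in %, unstratified / stratified by centre:

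| Centres | SD 0 | SD 0.2 | SD 0.3 | SD 0.5 | SD 0.7 |
|---|---|---|---|---|---|
| 30 | 80.0 / 79.4 | 80.4 / 81.1 | 78.5 / 80.3 | 74.1 / 79.6 | 70.5 / 79.5 |
| 60 | 79.3 / 78.2 | 79.3 / 79.0 | 77.1 / 78.5 | 74.9 / 79.7 | 68.6 / 78.4 |
| 100 | 80.2 / 79.3 | 77.7 / 76.6 | 79.1 / 79.7 | 74.1 / 78.4 | 69.0 / 78.2 |
| 150 | 79.9 / 77.4 | 79.1 / 77.8 | 77.6 / 77.4 | 75.8 / 78.2 | 67.6 / 76.6 |

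Gain from stratifying, in points, across the four centre numbers:

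- SD 0: −2.5 to −0.6
- SD 0.2: −1.3 to +0.7
- SD 0.3: −0.2 to +1.8
- SD 0.5: +2.4 to +5.5
- SD 0.7: +9.0 to +9.8

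The average unstratified hazard ratio is about 0.854 at SD 0.3, 0.861 at SD 0.5 and 0.870 at SD 0.7. The stratified one stays at about 0.85.

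**Step 3. Arithmetic check at SD 0.5, 30 centres.** The expected statistic is √1194/2 × |ln 0.861| = 17.28 × 0.1497 = 2.586. The simulated SD of the unstratified statistic is 0.952. Power = Φ((2.586 − 1.96)/0.952) = Φ(0.657) = 74.4%, against 74.1% simulated. Dilution of the hazard ratio therefore accounts for the loss.

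**Step 4. Type I error.** With hazard ratio 1 (30 or 100 centres, 2000 trials each, standard error about 0.5 points), the unstratified test rejects in about 4 to 5% of trials at SD 0.2 to 0.5 and in 2.8% at SD 0.7. Two single values stood higher: 6.2% unstratified (30 centres, SD 0) and 6.7% stratified (100 centres, SD 0.5). They follow no pattern, and a longer rerun of those two settings brought both close to 5%.

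**The case against.** **The article is silent; it does not say the test is unstratified.** This is a condensed article, and stratification of the test may be specified in the full protocol or SAP. That stands, and it is why the remedy may be a single clause. But the article does name a test, in the form of two curves, and gives centre no role. The point concerns that stated method.

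**Centre's absence from the covariate list proves nothing.** A reader might infer that centre was deliberately left out of the model. The documents do not support this: the list is for subgroup analysis, and the Cox adjustment set is not given.

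**The loss needs large centre differences.** SD 0.5 means a hazard ratio of exp(2 × 1.645 × 0.5) = 5.2 between centres at the 95th and 5th percentiles. Nothing in the article establishes a spread of that size. This stands, so any shortfall is conditional.

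**Marginal against within-centre effect.** The article does not say that 0.85 is a within-centre hazard ratio. If it is the marginal one, the unstratified test has its planned power, and the move to 0.86 is partly a change of estimand rather than bias. This also stands. In that case, though, the within-centre effect is larger than planned whenever centres differ, so the stratified test keeps its relative advantage at clear heterogeneity.

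**Follow-up can be changed.** Sample size and Interim analysis allow the duration to be altered if event rates or the risk reduction depart from assumption. That is partial protection. It adds power only if the event target rises above 1194, and it recovers by longer follow-up what an analysis choice could supply.

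**Stratifying can cost power.** True with many small centres and little heterogeneity, as the table shows. It is the reason for a pooling rule.

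**Conclusion.** The point holds as one of efficiency. The randomization stratum has no stated role in the named comparison, so the analysis as written gives away precision if centres differ. Under the assumptions above, the loss is about 0 to 2 points of power at SD 0.3 or less and about 2 to 6 points at SD 0.5. It reaches 9 to 10 points only at SD 0.7, which is an extreme case. Two separate simulations of 1200 trials per scenario gave the same direction and similar sizes.

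Two stronger readings are not supported. One is that the test is invalid or inflates false positives: the simulated error rates show the reverse, if anything. The other is that the trial falls short of 80% power: that depends on the between-centre variation, the number of centres and the estimand, none of which the article gives. The change is worth making because it is cheap, not because a defect in the result has been shown.

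**What to change.** In Data analysis, state that the primary log-rank test is stratified by centre and that the hazard ratio comes from a Cox model stratified the same way. Fix in advance how very small centres are pooled, for example by region, without reference to outcome or arm. Keep the unstratified log-rank test as a sensitivity analysis. State that the hazard ratio of 0.85 is meant as a within-centre effect, if that is the intention.

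The cost is wording only: no patients, visits or data. If centres do not differ, stratifying costs about 0.5 to 2.5 points of power, most with many small unpooled centres (2204/150 is about 15 patients each). Pooling should limit that. A random centre effect (frailty term) is an alternative if there are many small centres. If the full protocol or SAP already stratifies the test, a clause in Data analysis saying so resolves the point.
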